## Abstract

**Background:**

Treatment with programmed cell death receptor (PD-1) and programmed cell death ligand 1 (PD-L1) inhibitors is a promising strategy to lift tumour-induced immune response suppression. However, the current systemic treatment often causes autoimmune side effects. In more than 50% of squamous cell cervical cancer, PD-L1 expression is detected. Moreover, we observed high and interrelated rates of PD-L1 positive macrophages and regulatory T cells in metastatic lymph nodes of cervical cancer patients. As cervical cancer in general initially metastasizes to regional lymph nodes, local administration of durvalumab (a PD-L1 checkpoint inhibitor) at an early stage will deliver these antibodies exactly where they are needed, facilitating immune protection. This may result in a clinical benefit while reducing undesirable side effects.

**Methods:**

DURVIT is a non-randomized, single-arm, open-label, phase I study. Three escalating dose levels of intratumourally (i.t.) injected durvalumab will be tested, i.e. 5, 10 and 20 mg (three patients per dose level, with an additional three at the highest tolerated dose). The primary endpoint of this phase-I study is safety. Immune monitoring will consist of flow cytometric, immunohistochemical and functional T cell reactivity testing. The first patient has been included in this trial in November 2017.

**Discussion:**

Evidence of safety and biological efficacy of this locally administered checkpoint blockade may expand adjuvant therapy options for cervical cancer patients. Early metastatic spread of cervical cancer cells may thus be controlled in the draining lymph node basin, and beyond, and hopefully delay or even prevent the onset of disease recurrence.

**Trial registration:**

NTR6119, 1-nov-2016.

**Electronic supplementary material:**

The online version of this article (10.1186/s12885-018-4764-0) contains supplementary material, which is available to authorized users.

## Background

Cervical cancer is the fourth most common cancer in women worldwide and is caused by a persistent infection with high-risk human papilloma virus (HPV) types [1, 2]. The highest incidence of cervical cancer lies between 35 and 45 years of age [3]. Although vaccines to prevent cervical cancer are widely implemented, advanced stage cervical cancer is still an important cause of mortality among women worldwide [4].

The most important prognostic factor in early stage cervical cancer is the presence of metastatic tumour cells in the pelvic lymph nodes [5]. After radical hysterectomy and pelvic lymphadenectomy, women with early stage cervical cancer with negative lymph nodes have a 5-year survival rate of 80–90%, compared to a 5-year survival of 60–65% for patients with one lymph node metastasis [6, 7]. Adjuvant treatment in patients with lymph node metastasis and/or other risk factors is (chemo)radiation [8, 9]. However, adjuvant chemoradiation is associated with increased morbidity (with reported symptoms such as nausea, pain, vaginal tightness and urinary complaints) and impaired quality of life [10]. Of note, adjuvant (chemo)radiation in cervical cancer may also result in ovarian failure, and most patients diagnosed with cervical cancer are relatively young [11].

To improve the prognosis and quality of life of cervical cancer patients, novel adjuvant treatments are urgently needed. A highly promising area of research focuses on lifting tumour-induced immune suppression. Cancer cells employ various mechanisms to evade immune-mediated surveillance and elimination, which allows them to develop and spread unchecked. One of these strategies comprises upregulation of proteins on the cell surface that deliver inhibitory signals to cytotoxic T cells, the so-called immune checkpoints. Programmed cell death ligand 1 (PD-L1) is an example of such an immune checkpoint, and is upregulated in a broad range of cancers, including lung [12], renal cell [13–15], pancreatic [16–18], ovarian cancer [19] and hematologic malignancies [20, 21].

Several studies have reported on the upregulation of PD-L1 and/or PD-1 in cervical carcinoma and surrounding inflammatory cells [22–25]. Recently, we performed a retrospective study on primary tumours (*n* = 205) and paired metastatic lymph nodes (*n* = 127) from cervical cancer patients and showed PD-L1 expression by primary tumour cells as well as by tumour infiltrating and stromal CD163+ positive M2 macrophages [26]. In 54% of all squamous cell primary tumours (SCC) and in 14% of all adenocarcinomas (AC) PD-L1 positivity was observed in > 5% of the tumour cells. PD-L1 expression in tumour margins (i.e. at the tumour/stroma interphase) in SCC was related to favourable survival and most likely induced by IFNγ released by adjacent activated T cells. In SCC, diffuse PD-L1 expression was associated with poor prognosis as was the presence of PD-L1 positive macrophages in AC. Furthermore, we reported on the high and interrelated rates of PD-L1 positive myeloid cells and regulatory T cells (Tregs) in metastatic lymph nodes in patients with cervical cancer [27]. In a comparative study of the immune status of all dissected cervical tumour-draining lymph nodes in five patients, we described that immunosuppression (identified as low CD8+ T cell/ FoxP3+ Treg ratios) may precede actual metastasis, creating niches in the tumour-draining lymphatic catchment area [28]. These results led to the hypothesis that tumour-associated PD-L1 positive macrophages expand Tregs which subsequently migrate to down-stream lymph nodes to create immune suppressed metastatic niches [29].

These studies support the clinical exploration of immunotherapies aimed at counteracting the immunosuppressive microenvironment in the primary tumour and the tumour-draining lymph nodes by PD-1/PD-L1 checkpoint blockade. By facilitating a robust antitumour T cell response, immune therapy can break the cycle of immune suppression and metastatic spread.

Durvalumab is a human monoclonal antibody (mAb) of the immunoglobulin G1 kappa (IgG1κ) subclass that blocks binding of PD-L1 to PD-1 and CD80 (B7–1). To date, results of several trials with systemically administered durvalumab in patients with advanced or metastatic cancer show promising antitumour activity with durable responses [30]. Durvalumab was recently approved by the U.S. Food and Drug Administration for patients with locally advanced or metastatic urothelial carcinoma who have disease progression during or following platinum-containing chemotherapy [31].

The systemic treatment with PD-1 and PD-L1 inhibitors can cause severe autoimmune side effects [32]. In the current study durvalumab is administered locally, i.e. in the cervix. As cervical cancer initially metastasizes through regional lymph nodes, we believe that local administration of durvalumab at an early stage will deliver these antibodies exactly where they are needed. Our hypothesis is that local conditioning of the tumour and tumour draining lymph nodes (TDLN) in the neo-adjuvant setting will lead to both loco-regional and systemic immune activation.In this way, undesirable systemic side effects may be avoided. Additional interest in local administration of checkpoint inhibitors is raised by the fact that the locally administered medication is expected to be (systemically) effective at a lower dose, leading to a desirable decline in the expenses involved.

## Methods/design

### Study design

‘DURVIT’ is a non-randomized, single-arm, open-label, phase I study. Patients with cervical cancer who are scheduled for (radical) hysterectomy with lymph node dissection will be enrolled at the Amsterdam UMC (formerly: Academic Medical Center (AMC), Amsterdam). Two weeks before the patient is scheduled for surgical treatment, durvalumab (AstraZenecaBV) will be injected locally into the cervix (Fig. 1). Three doses of durvalumab will be tested in a 3 + 3 dose escalation design: 5, 10 and 20 mg intratumourally (i.t.) (Fig. 2). If no dose limiting toxicities (DLTs) or treatment related serious adverse events (SAEs) are observed in the 3 different dose cohorts (5, 10, 20 mg) and no clear (systemic) immunological responses are detected based on T cell levels and FACS immunomonitoring, we will add an extra dose cohort of 3 patients treated with 50 mg durvalumab i.t. based on the same criteria. The Common Terminology Criteria for Adverse Events (CTCAE) v4.03 will be used for the assessment of adverse events.

**Fig. 1 Fig1:**
[figure not shown]
DURVIT study timeline. SN = sentinel lymph node

**Fig. 2 Fig2:**
[figure not shown]
DURVIT study flowchart. DLT = dose limiting toxicity, SAE = serious adverse event, MTD = maximum tolerated dose

Pre-treatment archival formalin-fixed, paraffin-embedded (FFPE) tissue samples will be requested from centres where patients were diagnosed or had their primary treatment. Post-surgery tumour and lymph node material will be fixed and stored. To have a complete clinical characterization of the patients included in this study, we will perform the standard diagnostic HPV typing for our institution: the HPV Risk Assay (Self-Screen) [33]. Blood samples will be taken once during the screening period, at day 0 (prior to durvalumab administration, i.e. at baseline), at day 14 (at the time of surgery), after 4 weeks, and at 3 months after administration of durvalumab. Post-surgery biopsies of the removed tumour and sentinel and non-sentinel TDLN samples will be collected and processed as described previously [27].

The trial has been approved by the Institutional Review Board of the Academic Medical Center (AMC) and sponsored by the AMC, with funding from Stichting Vrije Universiteit Medical Center - Cancer Center Amsterdam (VUmc-CCA) and Astra Zeneca for the immunological tests (requested). Electronic data is submitted by the study staff via the online database CastorEDC. The study will be monitored by the Clinical Research Unit of the AMC. The first patient has been included in this trial in November 2017.

### Participants

The inclusion and exclusion criteria for the DURVIT-study are listed in Table 1.

**Table 1 Tab1:** DURVIT Inclusion/Exclusion criteria

Inclusion criteria	Exclusion criteria
1. Age > 18 years at time of study entry 2. Willing and able to undergo the planned study procedures 3. World Health Organization (WHO) performance status of 0 or 1 4. Written informed consent 5. Histologically confirmed cervical cancer of all histological types 6. Scheduled to undergo (radical) hysterectomy with lymphadenectomy 7. No indication of an active infectious disease: HIV, HCV and HBV negative 8. No history of autoimmune disease or systematic underlying disease which might affect immunocompetence 9. Adequate bone marrow function 10. Subjects must either be of non-reproductive potential or must have a negative urine pregnancy test before study entry 11. Ability of subject to understand Dutch language	1. Prior treatment with immunotherapy including therapeutic vaccines 2. Involvement in the planning and/or conduct of the study 3. Participation in a study with another investigational drug within 30 days prior to enrolment in this study 4. Major surgery within 28 days before inclusion (conization or biopsy is not major surgery) 5. Severe cardiac, respiratory, or metabolic disease 6. Use of oral anticoagulant drugs (except ascal) 7. Severe infections requiring antibiotics 8. Lactation or pregnancy 9. Current or prior use of immunosuppressive medication within 28 days before the first dose of durvalumab, with the exceptions of intranasal and inhaled corticosteroids or systemic corticosteroids at physiological doses, which are not to exceed 10 mg/day of prednisone, or an equivalent corticosteroid 10. Any prior Grade ≥ 3 immune-related adverse event (irAE) while receiving any previous therapy, or any unresolved irAE >Grade 1 11. Active or prior documented autoimmune disease within the past 2 years 12. Active or prior documented inflammatory bowel disease 13. History of primary immunodeficiency/allogeneic organ transplant/previous clinical diagnosis of tuberculosis/uncontrolled intercurrent illness 14. Receipt of live attenuated vaccination within 30 days prior to study entry or within 30 days of receiving durvalumab 15. Any condition that, in the opinion of the investigator, would interfere with evaluation of study treatment or interpretation of patient safety or study results

### Interventions

Dependent on the dose cohort, 5, 10 and 20 mg (and possibly 50 mg) of durvalumab, in a 4 ml dilution will be administered using a single syringe and a 27-gauge needle. The solution will be administered at room temperature and will be injected at 4 sites (1 mL/site) peri- and/or intratumourally, depending upon tumour location, visibility and size. The injection procedure is identical to the i.t. injections already performed in a standardized fashion for the sentinel lymph node procedure. The whole procedure will take approximately 15–30 min.

During surgery (day 14), patent blue will be injected intratumourally for identification of the sentinel lymph node. The detection of the sentinel node using a blue dye and/or radioactive tracer is a feasible technique in cervical cancer [34] and increasingly used in the treatment of cervical cancer patients.

### Outcome measurements

The primary outcome of this study is safety, by the evaluation of (serious) adverse events, in order to determine the maximum tolerated dose (MTD) durvalumab. Dose-limiting toxicities (DLTs) will be evaluated during the dose escalation phase of the trial. If ≥2 out of 3 patients or ≥ 2 out of 6 patients in the first dose cohort (5 mg durvalumab) experience a DLT, this study will be ended. A DLT will be defined as any grade 3 or higher toxicity that occurs during the DLT evaluation period. Toxicity that is clearly and directly related to the primary disease or to another etiology is excluded from this definition. Grading of DLTs will follow the guidelines provided in the Common Terminology Criteria for Adverse Events (CTCAE) version 4.03.

The following will be DLTs:Any grade 4 immune-related adverse event (irAE)Any ≥ grade 3 colitisAny grade 3 or 4 non-infectious pneumonitis irrespective of durationAny grade 2 pneumonitis that does not resolve to ≤ grade 1 within 3 days of the initiation of maximal supportive careAny grade 3 irAE, excluding colitis or pneumonitis, that does not downgrade to grade 2 within 3 days after onset of the event despite optimal medical management including systemic corticosteroids or does not downgrade to ≤ grade 1 or baseline within 14 daysLiver transaminase elevation > 8 × upper limit of normal (ULN) or total bilirubin > 5 × ULNAny ≥ grade 3 non-irAE, except for the exclusions listed in Additional file 1

The period for evaluating DLTs will be from the time of administration of durvalumab until 3 months afterwards.

Secondary outcomes include the analysis of the microenvironment and immune status of the primary tumour and the draining lymph nodes, as well as the systemic antitumour immune response. Tumour and TDLN single-cell suspensions, as well as peripheral blood mononuclear cells (PBMC), will be analysed by multiparameter FACS panels for frequency and activation state of dendritic cell subsets, myeloid derived suppressor cells, macrophages, effector-T cells and Tregs. Advanced 35-parameter CYTOF analyses will also be performed to delineate known as well as novel immune subsets. In this way, the effects of the loco-regional treatment with durvalumab will be ascertained.

State-of-the-art 7-parameter fluorescence immunohistochemistry (IHC) panels will be used to analyse lineage and activation markers for the same subsets as for the aforementioned flow cytometry panels. The use of pre- and post-treatment FFPE material will allow the precise analysis of the density, compartmentalization, and (co-)localization of specific subsets. All IHC parameters will be determined using fully automated analyses.

As an indication of the induction of local and systemic T cell immunity, IFNγ elispot assays after in vitro stimulation will be performed on TDLN single-cells and PBMC to ascertain pre- and post-treatment frequencies of HPV-specific T cells (against long peptide pools derived from the immunodominant region of HPV-16 E6). We will also assess HPV16 T cell reactivity in PBMC and small tumour and TDLN samples using an ultra-sensitive technique based on DNA-barcoded MHC multimers with a PCR-based read-out (in collaboration with [name] [name], Technical University of Denmark). The multimers will be complexed to synthetic peptides (9–10 aa, 1210 peptides in total) spanning the whole sequence of E2, E6, and E7.

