## Discussion

With a peak incidence between 35 and 45 years of age, patients diagnosed with cervical cancer are relatively young. In early stage cervical cancer, the percentage of relapses is 5% to 40% depending on lymph node metastasis and other risk factors [35]. The most common types of cervical cancer are squamous cell carcinoma (SCC) and adenocarcinoma (AC), which are known to be mostly HPV-16 and HPV-18 positive, respectively [36, 37]. We have previously reported on the expression of PD-L1 in SCC and AC [26]. Intratumoural injection of anti-PD-L1, in this case durvalumab, with the aim to specifically modulate the loco-regional environment is an innovative clinical approach for the treatment of cervical cancer. Evidence of safety and biological efficacy of this strategy will contribute to the design of novel adjuvant therapy options for cervical cancer patients. In this way early metastatic spread to the draining lymph node basin, and beyond, may be controlled and thereby the onset of disease recurrence may be delayed or even prevented.

Although blocking the PD-1/PD-L1 axis has been associated with improved survival in many cancer types, auto immune-related side effects are often reported (in up to 70% of patients) [38]. These findings are based on studies including patients with advanced stages of disease. In studies evaluating the safety of intravenous anti-PD-L1 in patients with different types of cancer, most reported side effects were fatigue, infusion reactions, rash, arthralgia, pruritus, diarrhoea and decreased appetite. Immune-related adverse events included rash, hypothyroidism and hepatitis [39, 40]. Local administration of low-dose checkpoint inhibitors may reduce these side effects.

Until now, there is only one study that has reported interim results on the effect of systemic anti-PD-1 or PD-L1 treatment in cervical cancer. Data show that pembrolizumab, an anti-PD-1 antibody, can have durable antitumour activity in patients with PD-L1-positive advanced cervical cancer [41]. The safety profile was consistent with that seen in other tumour types. Out of 24 treated patients there were 2 discontinuations due to grade 3 treatment-related AEs and no ≥ grade 4 treatment-related AEs were reported. Currently, several trials are in progress testing systemic anti-PD-1 or PD-L1 treatment in cervical cancer [42]. However, none of these trials concern the local administration of therapy.

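### Two HPV16-only T cell assays stand for HPV-specific immunity in a trial open to all histologies, and the planned HPV typing is not used in their analysis

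*Protocol article*

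**What the plan says.** All references are to the protocol article.

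- **Outcome measurements, elispot.** The assay is run "against long peptide pools derived from the immunodominant region of HPV-16 E6". Its purpose is "to ascertain pre- and post-treatment frequencies of HPV-specific T cells", and the result is offered as a sign that T cell immunity has been induced locally and systemically.
- **Outcome measurements, multimers.** "We will also assess HPV16 T cell reactivity in PBMC and small tumour and TDLN samples". The peptides cover E2, E6 and E7. No other HPV type is named for either assay.
- **Participants, Table 1.** Inclusion criterion 5 is "Histologically confirmed cervical cancer of all histological types". No criterion refers to HPV type.
- **Discussion.** Squamous cell carcinoma and adenocarcinoma are described as the most common types, "which are known to be mostly HPV-16 and HPV-18 positive, respectively".
- **Study design, text below the Fig. 2 legend.** Typing is planned, with this stated purpose: "To have a complete clinical characterization of the patients included in this study, we will perform the standard diagnostic HPV typing".
- **Analysis of secondary endpoints (immune parameters).** Immune cell subsets are compared before and after treatment with t tests, Mann-Whitney tests and repeated measures ANOVA. HPV type does not appear.

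**The concern.** Each choice is reasonable alone, but together they do not fit. A type-specific assay is labelled HPV-specific in a population that the article itself describes as mixed in HPV type. For a patient with an HPV-18 tumour, a flat HPV16 result says nothing about whether durvalumab induced immunity against that tumour. Pooling such patients with the rest pulls the mean before/after change toward zero.

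The Conclusion expects the immunoassays to help choose the dose and target population for later trials, and the Statistical analysis section tabulates by cohort. With three patients per dose level, a level that happens to hold few HPV16 tumours could be misread as a dose without immunological effect.

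**Working it through.** **The plan's own figure.** The article's only power calculation gives 6 patients at the maximum tolerated dose (Considerations for sample size). The difference is 0.33 × 38.1 = 12.57 points with SD 10.5. The one-sample normal formula, two-sided 0.05 and power 0.8, gives ((1.96 + 0.84) × 10.5 / 12.57)² ≈ 5.5, so 6. This reproduces the figure, but it concerns Treg frequency in the tumour, which is not an HPV16-restricted readout. It neither supports nor undermines the HPV16 assays; they have no power claim.

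**Inputs for the dilution.** The antigens, eligibility and purpose of typing are as cited above. The share q of enrolled patients with an HPV16-positive tumour is not given; 0.4 to 0.8 is assumed. The sizes of change are also assumed. The mean change is taken as zero in patients without an HPV16 tumour.

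**Dilution.** If the mean change in HPV16-positive patients is μ, the pooled mean is qμ + (1 − q) × 0 = qμ, that is 40% to 80% of μ.

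**Composition.** The expected number of informative patients among 6 is 6q. The chance that a cohort of 3 has no HPV16 tumour is (1 − q)³. The chance that at least one of three such cohorts has none is 1 − (1 − (1 − q)³)³: 52% at q = 0.4 and 2% at q = 0.8.

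**Illustrative power.** Simulated one-sample t test on the before/after change, two-sided 0.05. The 12 patients are three levels of 3 plus 3 more at the highest tolerated level (Abstract). The change in HPV16-positive patients has SD 1, with mean 1 for n = 12 and mean 1.5 for n = 6. The others have mean 0 and SD 0.3 or 1. The restricted test uses HPV16-positive patients only; fewer than two counts as no rejection.

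| q | 6q | (1 − q)³ | n = 12 pooled, others SD 0.3 | n = 12 pooled, others SD 1 | n = 12 restricted | n = 6 pooled, others SD 1 | n = 6 restricted |
|---|---|---|---|---|---|---|---|
| 0.4 | 2.4 | 22% | 0.26 | 0.20 | 0.37 | 0.15 | 0.23 |
| 0.5 | 3.0 | 13% | 0.39 | 0.29 | 0.49 | 0.22 | 0.33 |
| 0.6 | 3.6 | 6% | 0.52 | 0.40 | 0.60 | 0.30 | 0.44 |
| 0.7 | 4.2 | 3% | 0.64 | 0.52 | 0.69 | 0.41 | 0.55 |
| 0.8 | 4.8 | 1% | 0.74 | 0.65 | 0.77 | 0.53 | 0.66 |

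In every row restriction gains power despite the smaller n. At n = 12 the gain is about 3 to 11 points if the other patients vary little (SD 0.3) and 12 to 20 points if they vary as much as the HPV16-positive ones (SD 1). At n = 6 it is about 8 to 15 points.

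**The case against.** The strongest objection is that no sentence says the HPV16 assays are analysed in all patients. The analysis section speaks of immune cell subsets and names neither assay. Typing is tied to clinical characterization without excluding other uses, and choosing an analysis set for a secondary endpoint is often left to a statistical analysis plan, which is not shown. This stands in part: unrestricted pooling is the plain reading, not an explicit statement. It does not dispose of the point, because the mismatch lies in what the article does state: the antigens, the HPV-specific label, the eligibility and the expected HPV types.

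Four stronger readings are tempting, and the documents do not support them.

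- *Patients without HPV16 are counted as non-responders.* The article defines no responder or threshold for these assays; it speaks of frequencies before and after treatment.
- *A large power loss can be recovered.* With six patients all HPV16-positive and a 1.5 SD change, power would be 0.83, against 0.15 to 0.53 pooled. Restriction cannot supply six such patients; it reaches 0.23 to 0.66. The article also makes no power claim for this endpoint, and the pooled test of 12 is an illustration.
- *The decision to add the 50 mg cohort is biased.* That rule rests partly on T cell levels and FACS monitoring and names neither HPV16 assay. T cell levels are not defined, so a link is possible but not shown.
- *Restriction removes the confounding of dose with HPV type.* It does not. Chance imbalance is inherent in cohorts of three, and a cohort without HPV16 tumours would simply contribute no data. Only a display of HPV type by patient makes this visible.

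The FACS, CYTOF and immunohistochemistry readouts are not HPV16-restricted and still cover every patient.

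**Conclusion.** The point holds in a limited form. Both antigen-specific assays see only HPV16-directed T cells, the article expects part of its eligible population to have tumours of another type, and it does not use its own typing to interpret these readouts. Read as written, the mean before/after change is about q times its value in HPV16-positive patients: 40% to 80% under the assumed range. The associated power loss is modest and depends on the assumed effect and variability.

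The result rests on a mean change near zero in patients without an HPV16 tumour. Some of them may carry HPV16 memory from an earlier infection; that response would not be tumour-specific, which is a further reason to report them separately. The primary safety endpoint and the maximum tolerated dose are untouched. This is a worthwhile correction to a secondary, exploratory analysis and not a threat to the trial.

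**What to change.** In the analysis section for immune parameters, state that the main before/after analysis of the HPV16 elispot and multimer readouts is made in patients whose tumour is HPV16-positive by the typing already planned. Report the remaining patients separately. List HPV type per patient by dose level, so that a cohort with few or no HPV16 tumours is not taken as evidence of no dose effect. In Outcome measurements, call the readout HPV16-specific.

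The cost is a few sentences and a smaller n for this endpoint: an expected 2.4 to 4.8 of six patients under the assumed range. No extra patients are needed, and no extra tests, provided that the planned assay reports HPV16 separately; the article calls it typing but does not list the types reported. The rule should be fixed before the assay results are seen, so that the restriction is not a post hoc subgroup.
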